#### Follow-up

Follow-up self-report surveys at 3 and 6, months using the AUDIT-C tool were conducted via text message. Three text-backs were required at 3 and 6 months follow-up. At the 9 month follow-up time point participants were asked via SMS messaging to text back to confirm their email address (which was provided at baseline). The total number of text-backs required was 7 text messages and participants were aware that they bear the cost involved. For participants on pre-pay plans this would cost a maximum of NZ$1.40. In order to acknowledge this cost and their participation in the study, treatment and control group participants receive a shopping voucher at the time of recruitment.

The 12-month web-based survey developed in LimeSurvey (open source software) included the full 10-item AUDIT as well as questions to gather self-reported data on health and social outcomes and legal consequences of heavy drinking during the follow-up period. Participants were asked two sets of ‘drinking consequences’ drawn from the GENACIS project (http://www.genacis.org/11) [39]. These comprised seven questions relating to possible alcohol-related ‘harms’ in the previous 12 months and seven questions relating to possible alcohol-related ‘troubles’. They were also asked questions about their alcohol-related healthcare service seeking behaviours, their current feeling about their readiness to change using a visual analogue scale [40], their experience with hangovers, and their experience of being in the study (i.e. the ‘good things’ about being in the study and what they ‘liked least’). Participants who were unable to complete the web-survey or preferred an alternative, had the survey administered by phone.

To encourage participants to reply to text message questions at the 3, 6, and 9 month follow-up points and to complete the online survey at 12 months, an incentive was offered. As part of the text message communication at each of the follow-up time points, participants were advised they would be eligible for a prize draw for a $200 supermarket voucher. Once each follow-up period had been completed for all participants, one participant was selected randomly from all those who had completed follow-up for that time-point. Four different participants each received a voucher.

Information regarding injuries during follow-up will be obtained via probabilistic record linkage to national databases on injury-related insurance claims (Accident Compensation Corporation) and Ministry of Health data on hospital discharges, ambulatory care visits and deaths at 24 months following the index admission. In general, approximately 24 months following an event is required to assure completeness of injury data recorded in routine databases with confirmed cause of death information for fatal injury events.

#### Screening of text-backs from participants

A specification was built into the intervention content delivery system to identify text responses from participants indicating they wish to stop receiving text messages. On receipt of such a message, an automated response acknowledging receipt of the participant’s message was sent and then all subsequent text messages were automatically stopped. Participants who requested to be withdrawn from the study had no further data collected.

Participants who sent an unsolicited text-back were sent an automated text message as follows: ‘From YourCall: This is an automated reply to your txt. If u are in an emergency situation, call 111’.

In addition to the above, a daily report was generated detailing any unrecognised responses received from participants. This was reviewed by a dedicated study team member who determined the appropriate level of action, the details of which were recorded in the ‘Text Response Register’. The levels of action included:No action required (e.g. conversational or acknowledgement text-backs)Action required on a study-related matter (e.g. participant asking to stop messages in a way that was not recognised by the computer system)Action required on another matter (e.g. message indicating personal distress; response was determined on a case-by-case basis and reviewed by the Principal Investigator

### Sample size calculations

Based on the published literature on distribution in AUDIT-C scores in previous trials, we aimed to recruit approximately 570 participants to this study. This was based on a conservative estimate that 25% of patients screened will have AUDIT scores in the eligibility range for moderately hazardous drinking and a 75% participation rate. We anticipated that 400 (70%) of these participants would complete 12 months of follow-up. This sample size provides 80% power to detect a true difference of 7.5% (i.e., a mean difference between groups in AUDIT-C scores of 0.51) at the 0.05 level of significance.

As designed, this is a large trial relative to most alcohol intervention studies conducted previously. By recruiting patients from all major trauma-admitting hospitals in the greater Auckland region, we expected to recruit sufficient participants to determine effects on alcohol misuse and related harms (including injury recurrence) with adequate statistical power in a resource efficient manner.

The study also aimed to recruit as many Māori participants as possible with a minimum of 20% of the total sample, a situation deemed feasible given the ethnic distribution in the Auckland region. This sample size was expected to provide good power to test consistency in effect for Māori compared with non-Māori.

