**Fig. 1 Fig1:**
[figure not shown]
CONSORT diagram for YourCall™ trial

Will have reduced hazardous drinking at 3, 6 and 12 months follow-up as assessed by the AUDIT-C score (primary outcome at 3 months)Will have fewer subsequent medically attended injuries (identified through record linkage to national databases), andWill experience less adverse health and social outcomes, e.g., sexual harm, mental health problems, and legal consequences of heavy drinking (identified through a self-report survey at 12-months follow-up).

We also hypothesise that the effectiveness of the intervention (as measured above) will be similar among Māori and non-Māori.

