### Statistical methods

Statistical analyses of the data gathered in this trial are being performed using SAS version 9.4 (SAS Institute Inc. Cary NC). All participants considered for eligibility for the study will be accounted for in analyses. The principal evaluations of interest in this study subscribe to the ‘intention to treat’ principle, i.e. all participants are analysed in the group to which they were randomised, regardless of whether they discontinued or deviated from the protocol. However, no outcome data were collected from participants who withdrew, beyond their withdrawal day.

This trial did not include plans for interim analyses or stopping guidelines. Accordingly, analyses are being performed after 12 month follow-up has been completed. Secondary outcome data regarding subsequent injury events are expected to require a minimum of 24 months to lapse from recruitment given the time required to get cause of death information in national mortality databases. Missing data are not imputed. All statistical tests are two-tailed with a 5% significance level maintained throughout the analyses.

A CONSORT trial profile will summarise the number of participants who were considered, fulfilled eligibility criteria, reasons for exclusions, randomised, withdrawn, and lost to follow-up. Data for the intervention and control groups are being summarised with respect to baseline demographic variables (age, sex, ethnic group), employment, education, mobile phone usage, cigarette smoking, recreational drug usage, self-reported role of alcohol in the injury, mechanism of injury, nature of injury, injury intent, baseline AUDIT, and AUDIT-C mean scores.

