#### Analysis of primary outcome

Mixed-effects model for repeated measure (MMRM) method is being used to analyse the primary outcome. The model assesses treatment group, visit, group and visit interaction, the randomisation variables of age, gender, ethnicity and hospital centre (three centres) as fixed effects; baseline AUDIT-C measure as a covariate; and participant as a random effect. The primary outcome is determined by the treatment effect at three months. Variance (co)variance structures are considered to model the within-subject errors, including, but not restricted to, unstructured, compound symmetry, autoregressive AR(1) structures. The Kenward-Roger method is being used to estimate the denominator degrees of freedom for fixed effects. Per Protocol analysis will be performed on the primary outcome as a sensitivity analysis. The per protocol population comprises all randomised participants excluding those who had protocol violations. When appropriate, post-hoc analyses will be conducted.

To assess the effectiveness of the programme for Māori and non-Māori, the analysis of the primary outcome will be repeated with the treatment and ethnicity (Māori vs non-Māori) interaction added to the model. As the study is not powered to test this interaction, the interpretation of this analysis will be made with caution.

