## Discussion

An effective m-health intervention has the potential to overcome some of the commonest barriers to addressing alcohol problems identified in the trauma care setting. This protocol provides detailed information regarding the design and methods of a randomised controlled trial that aims to evaluate the effectiveness of YourCall™, an SMS-text message intervention to support injured patients reduce harmful drinking patterns. The mHealth intervention approach has particular appeal in this context given the high-degree of scalability at relatively low cost per person and the ability to reach low-income groups at least partly mitigating risks of inequitable access to care and support services in the post-injury rehabilitation phase.

Acknowledging the structural determinants that influence and sustain inequities in alcohol consumption and related harm in many populations [24], we also aim to assess the equivalence of the effectiveness of the intervention among Māori and non-Māori participants in the trial. There is an increasing body of research attesting to the possibility that some alcohol-related interventions may inadvertently increase inequities in alcohol consumption and alcohol-related health outcomes [24].

Although the YourCall™ intervention lacks the ‘face to face’ interactivity of traditional brief interventions using motivational interview techniques, it incorporates other attributes that can enhance effective communication, e.g., confidential, personalised and tailored text messages which can be reinforced at periodic intervals, simulating booster interactions [28, 43–45]. A recent review of standard brief interventions for young adults in emergency department suggests that at least one therapeutic contact some distance from the event is associated with more successful outcomes [45].

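### The sample size section claims good power to compare the effect in Māori and non-Māori; the analysis section says the trial is not powered for this, and the design's figures support the analysis section

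*Protocol article*

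**What the plan says.** The protocol article speaks to the Māori question in four places.

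- **Design and hypothesis** (list following Fig. 1): "We also hypothesise that the effectiveness of the intervention (as measured above) will be similar among Māori and non-Māori".
- **Sample size calculations**: after setting a minimum Māori share of 20%, it states "This sample size was expected to provide good power to test consistency in effect for Māori compared with non-Māori". No power figure or size of difference is attached.
- **Analysis of primary outcome**: the primary mixed model is to be refitted with a treatment-by-ethnicity (Māori or non-Māori) interaction, followed by "As the study is not powered to test this interaction, the interpretation of this analysis will be made with caution".
- **Discussion**: "we also aim to assess the equivalence of the effectiveness of the intervention among Māori and non-Māori participants in the trial".

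The design figures are in Sample size calculations: "we aimed to recruit approximately 570 participants to this study"; "We anticipated that 400 (70%) of these participants would complete 12 months of follow-up"; and "This sample size provides 80% power to detect a true difference of 7.5% (i.e., a mean difference between groups in AUDIT-C scores of 0.51". Allocation is 1:1 (Design and hypothesis). Statistical methods adds: "All statistical tests are two-tailed with a 5% significance level maintained throughout the analyses".

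**The concern.** The two statements about power concern the same comparison in the same trial, and they cannot both stand. Neither is superseded text.

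It matters which one a reader carries away. Equitable benefit for Māori is part of the trial's overall goal in the Background, the interaction is announced in the abstract, and the Discussion warns that some alcohol interventions may widen inequities. The hypothesis is framed as similarity and the Discussion's aim as equivalence, whereas the analysis described looks for a difference. When such an analysis has low power, a non-significant result is likely even if one group gains nothing. A reader who trusts the good-power sentence would give that result more weight than it can bear.

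**Working it through.** **Inputs from the article.** Two-sided 5% level; 80% power for 0.51 points; 570 recruited, 400 completing; 1:1 allocation; Māori share at least 20%.

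**Assumptions.** The article gives no SD, so it is back-solved. SDs are taken as equal in the two ethnic groups, with 1:1 allocation within each. The interaction examined is 0.51 points, meaning the whole planned effect is present in one group and absent in the other. The article names no size for this difference. Normal approximation throughout.

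**1. The plan's own figures.** 570 × 0.70 = 399, which agrees with 400. The 80% power cannot be checked independently without an SD. With 200 per arm it implies

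SD = 0.51 / (2.8016 × √(2/200)) = 1.82,

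where 2.8016 = 1.960 + 0.842. The main-effect standard error is then 1.82 × √(2/200) = 0.182.

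**2. Standard error of the interaction.** With N analysed and Māori share f,

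SE_int = SD × √(4/(N·f) + 4/(N·(1−f))), so SE_int / SE_main = 1/√(f(1−f)).

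At f = 0.20 the ratio is 1/√0.16 = 2.5. With 80 Māori and 320 non-Māori, SE_int = 1.82 × √(4/80 + 4/320) = 0.455.

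**3. Power for an interaction of 0.51.** Power = Φ(0.51/SE_int − 1.96) + Φ(−0.51/SE_int − 1.96). The detectable interaction at 80% power is 2.8016 × SE_int.

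| Analysed | Māori share | SE_int | Power for 0.51 | Detectable at 80% power | 95% CI half-width |
|---|---|---|---|---|---|
| 400 | 20% | 0.455 | 20% | 1.27 | 0.89 |
| 400 | 30% | 0.397 | 25% | 1.11 | 0.78 |
| 570 | 20% | 0.381 | 27% | 1.07 | 0.75 |
| 570 | 30% | 0.333 | 34% | 0.93 | 0.65 |

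For an interaction of half that size (0.255), power at 20% Māori is 9% (N = 400) or 10% (N = 570).

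**4. Dependence on the SD.** If the overall test has 80% power for 0.51 at the number analysed, interaction power at f = 0.20 is 20% whatever the SD, because 0.51/SE_int = 2.8016/2.5 = 1.12. If N = 400 is held and the SD varied instead, power is 27% at SD 1.5 and 16% at SD 2.17.

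**5. Baseline adjustment.** The model adjusts for baseline AUDIT-C. If 1.82 is an unadjusted SD and the baseline–outcome correlation is r (assumed 0.5 to 0.7), the residual SD is 1.82 × √(1 − r²), or 1.58 to 1.30. With 20% Māori, power becomes 25% to 35% at N = 400 and 34% to 47% at N = 570. The most favourable combination tried (570 analysed, 30% Māori, r = 0.7) gives SE_int = 0.238 and power 57%. At N = 400 with 20% Māori, 80% power would need covariates to remove 1 − (1/2.5)² = 84% of the variance.

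**6. Number needed.** For 80% power on an interaction of 0.51 with 20% Māori: (2.8016 × 1.82/0.51)² × (4/0.2 + 4/0.8) = 100 × 25 = 2,500 analysed.

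**The case against.** The section that governs the analysis already discloses the lack of power and promises caution, and the sample size sentence is in the past tense, recording a planning expectation. That is fair: someone working only from the statistical methods would not be misled. It does not remove the conflict, because the article publishes the expectation as a property of the design, and the design's figures do not bear it out.

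A reader might go further and infer that a non-significant interaction will be declared similarity or equivalence. The documents do not support that. No section states such a rule, the stated intention is cautious interpretation, and the refitted model can yield both group-specific effects, not only a test. An equivalence margin or interval criterion is commonly left to an analysis plan, which is not shown here, so its absence is not a finding.

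It is also fair that 20% is the low end. It applies the 12-month completer count to a 3-month outcome and takes the minimum Māori share, although the trial sought to recruit more. It also makes no allowance for precision gained by covariate adjustment if the implied SD is unadjusted. The figure should be given as a range. No part of the range examined reaches 80%.

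**Conclusion.** The point stands as a wrong statement of power contradicted elsewhere in the same article. For an interaction as large as the whole planned effect, power is about 20% with 400 analysed and 20% Māori, and about 27% to 34% with 570 analysed and 20% to 30% Māori. It is higher, but still well below 80%, under plausible baseline adjustment. The detectable interaction with 20% Māori is about 1.3 points (N = 400) or 1.1 (N = 570), which is 2.1 to 2.5 times the planned main effect.

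These figures rest on the back-solved SD, equal SDs, balanced allocation within ethnic groups and the chosen interaction of 0.51. The contradiction itself rests on none of them.

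Given the similarity and equivalence framing, a non-significant interaction could not by itself support either conclusion. This limits what the result can show; it is not a charge that the plan intends to misreport it. The primary comparison and its sample size are unaffected.

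**What to change.** In Sample size calculations, replace the good-power sentence with the power range above and its assumptions, so that it agrees with the section on analysis of the primary outcome.

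State that the Māori question will be answered by the 3-month interaction estimate and by the Māori and non-Māori effects, each with a 95% confidence interval. State also that a non-significant interaction will be reported as inconclusive, not as similarity or equivalence.

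Do not add an equivalence margin at this stage. The article says analysis follows completion of the 12-month follow-up and that the primary outcome is already being analysed and presented, so a margin chosen now would be post hoc.

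The cost is a change of wording, and a stated power that is less favourable than the present sentence suggests.

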### Data collection and management

The study database was constructed in Oracle. Participant data was collected by research assistants using password protected iPads. Case report form (CRF) data are imputed and validated using eCRFs screens on the study website. Validation rules for each CRF were specified by the study manager, in association with the NIHI data manager. These rules included range checks so that inaccuracies in data collection could be identified early. A query was raised as soon as any values entered were outside the allowed range or if data were missing. As soon as a query was raised, the research assistants who collected and entered the data resolved the issue and amended the electronic CRFs. The management of all databases associated with this trial was undertaken by the data management and information technology groups at the NIHI. The database was regularly backed up and password-protected, with differing levels of access for different research staff depending on their roles and responsibilities.

### Study monitoring and quality control

The Study Steering Committee was responsible for the design of the study, recruitment and training of research assistants, development of the analysis plan, analysis and write of the study, and the dissemination of study findings. The members of this committee included: SA (principal investigator), RW (named investigator [NI]), BK (NI, project manager), PR (NI), GS (NI), MW (NI), VT (NI), IC (NI), SS (NI, lead researcher, project coordinator).

The coordinating centre, under the guidance of the Study Steering Committee was responsible for the overall coordination of the study including: the preparation and distribution of study materials, investigator meetings, registration and randomisation services (undertaken by NIHI), data management, achievement of recruitment targets, data collection and processing (in conjunction with NIHI), developing the intervention delivery system (automated text messages), adherence to the study protocol, statistical analysis, data quality, regulatory reporting requirements (ethics, funders), and the dissemination of findings from the study. The team included the following personnel: the project manager (BK), the project coordinator (SS), a data manager, a senior IT developer, a biostatistician, and a data services specialist.

Based on an assessment by the Health Research Council of New Zealand when the study was funded, the YourCall™ trial was deemed to not require an independent Data Monitoring Core Committee [41]. An external independent trial monitor was responsible for implementing the procedures documented in a Study Monitoring Manual. Each recruitment site and the coordinating centre was monitored to ensure that trial site staff conducted, recorded, and reported the trial according to the Protocol, the Manual of Procedures and The International Conference on Harmonisation of Technical Requirements for Registration of Pharmaceuticals for Human Use Good Clinical Practice guidelines [42]. Monitoring visits provided an opportunity for training, for discussion of trial issues, and for the establishment of good working relationships between trial personnel.

This study did not have an ‘endpoint adjudication committee’. No interim analyses were planned and the secondary injury outcomes were obtained after these were collated in routinely collected data in national databases.

### Reporting of adverse events for this trial

Adverse events will be reported and categorised with respect to their likely relationship to the intervention (i.e., definitely, possibly, not related). Adverse events that might be reasonably related to SMS text messaging include hand or finger pain, or involvement in an accident as a result of sending or receiving a text relating to the study. No specific provisions were made for ancillary or post-trial care, or for compensation to those who suffer harm from trial participation. New Zealand’s accident compensation scheme provides 24-hour no-fault personal accident insurance cover.

### Statistical methods

Statistical analyses of the data gathered in this trial are being performed using SAS version 9.4 (SAS Institute Inc. Cary NC). All participants considered for eligibility for the study will be accounted for in analyses. The principal evaluations of interest in this study subscribe to the ‘intention to treat’ principle, i.e. all participants are analysed in the group to which they were randomised, regardless of whether they discontinued or deviated from the protocol. However, no outcome data were collected from participants who withdrew, beyond their withdrawal day.

This trial did not include plans for interim analyses or stopping guidelines. Accordingly, analyses are being performed after 12 month follow-up has been completed. Secondary outcome data regarding subsequent injury events are expected to require a minimum of 24 months to lapse from recruitment given the time required to get cause of death information in national mortality databases. Missing data are not imputed. All statistical tests are two-tailed with a 5% significance level maintained throughout the analyses.

A CONSORT trial profile will summarise the number of participants who were considered, fulfilled eligibility criteria, reasons for exclusions, randomised, withdrawn, and lost to follow-up. Data for the intervention and control groups are being summarised with respect to baseline demographic variables (age, sex, ethnic group), employment, education, mobile phone usage, cigarette smoking, recreational drug usage, self-reported role of alcohol in the injury, mechanism of injury, nature of injury, injury intent, baseline AUDIT, and AUDIT-C mean scores.

